### Data analysis

The comparability of both groups on prognostic and outcome variables at baseline will be analysed using two-sample t-tests in data with a normal distribution, Wilcoxon tests in non-parametric data and Chi-square tests in nominal data. An intention-to-treat analysis will be utilised in which all participants will be analysed in the group to which they were originally assigned. Differences between the groups over time are measured by Mann-Whitney-U-test. The influence of baseline differences on outcome measurements will be assessed in a multivariable linear regression analysis. A regression analysis of the factors being positive or negative predictors will be conducted based on covariates measured at baseline. Statistical significance is set at p < 0.05.

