### Sample size calculation

Based on the results of our previous case series, inter-group difference in improvement of 0.9 points on the PSFS is to be used [71]. This difference is also clinically relevant as it displays an improvement of approximately 20% compared with an expected PSFS baseline score of 5 points. We used a standard deviation of 1.5 points, alpha was set at 0.05 and the power was set at 0.9. In each group, 48 patients are needed. Anticipating a 10% drop-out rate, the required sample size was set at 106 patients to be randomised.

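### The one named between-group test, Mann-Whitney, neither adjusts for baseline PSFS nor combines the follow-up visits; a baseline-adjusted linear model as the primary comparison would use the same data better

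*Protocol article*

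**What the plan says.** The Data analysis section gives one sentence to the treatment comparison: "Differences between the groups over time are measured by Mann-Whitney-U-test". It names no covariate and no visit, and does not say whether the test is applied to scores or to changes from baseline. The test is not labelled primary; that is inferred because no other between-group outcome test is named.

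Two regressions follow. The first is described thus: "The influence of baseline differences on outcome measurements will be assessed in a multivariable linear regression analysis". The second looks for predictors: "A regression analysis of the factors being positive or negative predictors will be conducted based on covariates measured at baseline". Neither is designated as the treatment comparison.

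Under Primary outcome, PSFS is a 0-10 scale recorded at baseline, post-treatment, 6 months and 12 months. The Sample size calculation works on a difference in means: "inter-group difference in improvement of 0.9 points on the PSFS is to be used", and "We used a standard deviation of 1.5 points, alpha was set at 0.05 and the power was set at 0.9". It concludes: "In each group, 48 patients are needed".

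**The concern.** The stated test fits the design and the sizing poorly in three ways.

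- **Baseline.** PSFS is measured before randomisation, but the named test does not adjust for it. Where baseline and follow-up are correlated, adjustment removes variance from the comparison.
- **Visits.** Mann-Whitney compares two independent sets of single values. It can be run at one visit or on one change score. It cannot estimate a treatment effect jointly over three post-baseline visits, which the phrase about differences over time suggests is wanted.
- **Scale.** The trial is sized to detect 0.9 PSFS points, which the article calls clinically relevant. A rank test does not of itself give a mean difference to set against that figure.

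At stake are power that could be had without extra patients, and a main result readable in the units of the design. There is also a question of precedence: the rank test and the regression could disagree, and the article does not say which decides.

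**Working it through.** **Inputs from the Sample size calculation.** Δ = 0.9, SD = 1.5, alpha 0.05 (sidedness not stated), power 0.90, 48 per group, 106 randomised with 10% drop-out. After that loss, 106 × 0.9 / 2 = 47.7 per arm, so 48 per arm is used throughout.

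**Inputs assumed.** The article gives no baseline/follow-up correlation r; 0.3, 0.5 and 0.7 are used. It does not say whether 1.5 is the SD of a score or of change, so both readings are run, with equal variances at baseline and follow-up.

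**Step 1: reproduce the plan's figure.** n per group = 2(z_alpha + z_power)²(SD/Δ)².

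- One-sided 5%: 2(1.645 + 1.282)²(1.5/0.9)² = 47.6, so 48. This matches.
- Two-sided 5%: 2(1.960 + 1.282)²(1.5/0.9)² = 58.4, so 59. This does not match.

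**Step 2: separate sidedness from the choice of test.** At 48 per arm, unadjusted:

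- one-sided, normal formula: 90.2%;
- two-sided, normal formula: 83.6%; by noncentral t: 82.9%;
- two-sided Mann-Whitney, effective n = 48 × 3/π = 45.8: 81.9% (simulated 81% to 82%).

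Most of the fall from 90% comes from sidedness. Ranks in place of a t-test cost only about 1 to 2 points.

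**Step 3: effect of baseline adjustment.** Residual SD after ANCOVA:

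- if 1.5 is the SD of a score: 1.5 × √(1 − r²) = 1.43, 1.30, 1.07 for r = 0.3, 0.5, 0.7;
- if 1.5 is the SD of change: 1.5 × √((1 + r)/2) = 1.21, 1.30, 1.38.

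By the normal formula, two-sided at 48 per arm, power is 87%, 92%, 98% on the first reading and 95%, 92%, 89% on the second. Simulation under normal data (8,000 runs per setting, two-sided 5%) gives:

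| SD 1.5 refers to | r | Mann-Whitney on follow-up | Mann-Whitney on change | ANCOVA |
|---|---|---|---|---|
| score | 0.3 | 82% | 67% | 86% |
| score | 0.5 | 81% | 81% | 92% |
| score | 0.7 | 81% | 95% | 98% |
| change | 0.3 | 92% | 81% | 95% |
| change | 0.5 | 81% | 81% | 91% |
| change | 0.7 | 60% | 81% | 88% |

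ANCOVA is ahead of both rank tests in every row, by about 3 points (98% against 95%; 95% against 92%) to 28 points (88% against 60%). Which rank version does better turns on r: follow-up scores at 0.3, change scores at 0.7.

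**Step 4: the same result as sample size.** For 90% power, two-sided, ANCOVA needs 54, 44 and 30 per arm (1.5 as SD of a score) or 38, 44 and 50 (SD of change). The unadjusted normal formula needs 59, and Mann-Whitney about 59 × π/3 = 62.

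**Not computed.** These figures are for ANCOVA at a single visit. Any further gain from a repeated-measures model needs between-visit correlations, which the article does not give.

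**The case against.** The strongest reply is that the article does use baseline. The sizing speaks of improvement, so Mann-Whitney on change scores is a natural reading, and the next sentence plans a linear regression on baseline differences that could yield an adjusted difference in points. This stands against any claim that the plan ignores baseline PSFS. What remains is that the named test does not adjust for it, and that the regression is given a different job.

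Other stronger readings are tempting, and the article does not support them:

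- *The rank test is why the trial falls below 90% power.* Step 2 shows it is not. The shortfall also presumes a two-sided test, which the article does not state; that is a separate matter.
- *No effect estimate will be reported.* The article is silent. A Hodges-Lehmann shift with an interval could accompany the rank test, the regression could supply a mean difference, and an analysis plan may say so.
- *A test that drops missing patients contradicts intention-to-treat.* The article promises that "all participants will be analysed in the group to which they were originally assigned", which concerns group assignment. Missing-data handling may sit in an analysis plan. A mixed model also leaves out patients with no post-baseline value, and keeps more patients only if those who drop out supplied an earlier visit.
- *The change is free.* It needs no patients or data, but it adds assumptions.

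Mann-Whitney is also a defensible choice on a bounded scale. That supports keeping it as a check. It is a weaker reason for making it the main comparison, since the article already accepts linear regression for its outcome measurements.

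**Conclusion.** The point holds as a worthwhile, inexpensive improvement; the plan is not in error here. The only named between-group test is unadjusted, handles one value per patient, and is off the scale of the 0.9-point target.

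A single-visit ANCOVA gains about 3 to 28 percentage points of power over Mann-Whitney across the settings tried. At r = 0.5 it takes a two-sided test from about 81% to about 92% under either reading of the SD.

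The size rests on 48 per arm, two-sided 5%, normal data, equal variances over time, and an assumed r between 0.3 and 0.7. It can be small where change scores are used and r is high, or where follow-up scores are used and r is low.

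**What to change.** In the Data analysis section, designate a baseline-adjusted linear model of PSFS as the primary treatment comparison, in one of two forms:

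- ANCOVA at a named primary time point, with treatment and baseline PSFS; or
- a linear mixed model over post-treatment, 6 and 12 months, with baseline PSFS, treatment, visit and treatment-by-visit, and the primary contrast taken at a named visit.

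Report the adjusted mean difference in PSFS points with its 95% CI, to be read against 0.9. Keep Mann-Whitney as a sensitivity analysis, stating the visit and whether it uses scores or change. State that the planned regressions on baseline differences and predictors are supportive.

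The cost is wording: no extra patients, visits or data. The trade-off is reliance on linearity and approximate normality of residuals on a bounded 0-10 scale and, for the mixed model, on missing-at-random and a covariance structure. The retained rank test partly checks the distributional assumption; it does not check missing-at-random.

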### Baseline assessment and randomisation

After eligibility has been confirmed, patients will be informed about the study comparing two treatments that are widely used in physiotherapy. After obtaining written informed consent, baseline measurements will be performed (see next paragraph). Participants will then be randomised using block allocation with a block size of four, to receive either movement control or general exercise. Randomisation is concealed and performed by an independent assistant at the School of Health Professions at the Zurich University of Applied Sciences via telephone.

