### Treatment effect modifiers

The following relevant covariates will be recorded in order to allow them to be controlled for in the analysis of this study. Movement control and endurance are addressed in the two treatment groups and are expected to modify treatment effect.

**Movement control impairment **of the lumbar spine is assessed using 6 tests described in the backgrounds section [65]. Post-treatment the test will be recorded on videotape. The evaluation of video footage will be carried out by a specially trained physiotherapist who will be blinded to the treatment allocation and data from previous measurements.

**Endurance of lumbar and abdominal muscles **is assessed using static isometric strength tests for trunk extension and for trunk flexion pre- and post-treatment [66,62].

**Fear avoidance beliefs **will be measured with the self-report Fear-avoidance beliefs questionnaire for physical activities and work developed by Waddell et al [67,68]. The validated Swiss German Version will be used, allowing prediction of treatment outcome [67] It will be administered at baseline.

Patient's regular use of **home exercises **will be assessed at 6 and 12 months follow-up.

**Personal characteristics **(age, gender, previous episodes of back pain) will be collected at baseline.

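### Baseline significance tests and a regression framed around baseline differences tie adjustment to chance imbalance; name the adjusted model, including baseline PSFS, in advance

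*Protocol article*

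**What the plan says.** Four statements in the Data analysis section of the protocol article bear on this point.

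- Baseline tests: "The comparability of both groups on prognostic and outcome variables at baseline will be analysed using two-sample t-tests in data with a normal distribution", with Wilcoxon and chi-square tests for other types of data.
- Group comparison: "Differences between the groups over time are measured by Mann-Whitney-U-test". This test takes no covariates.
- Regression on imbalance: "The influence of baseline differences on outcome measurements will be assessed in a multivariable linear regression analysis". No covariate is named.
- Predictor regression: "A regression analysis of the factors being positive or negative predictors will be conducted based on covariates measured at baseline". Again no covariate is named, and the purpose is different.

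The section Treatment effect modifiers introduces its list with "The following relevant covariates will be recorded in order to allow them to be controlled for in the analysis of this study". The list covers movement control, trunk endurance, fear-avoidance beliefs, home exercise, age, gender and previous episodes. Baseline PSFS is not on it. Home exercise is, although it "will be assessed at 6 and 12 months follow-up", that is, after randomisation.

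On allocation, the section Baseline assessment and randomisation says "Participants will then be randomised using block allocation with a block size of four, to receive either movement control or general exercise". It describes allocation as concealed and mentions no stratification factor.

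**The concern.** With concealed random allocation the null hypothesis of every baseline test is true by design. A significant result is a chance finding, and a non-significant one does not show that a variable can safely be ignored. What makes a covariate worth adjusting for is how strongly it predicts the outcome, not how far the arms happen to differ on it.

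The article defines its regression by reference to baseline differences, and the tests are the only means it gives of identifying such differences. Read together, the sentences suggest a model whose content is settled after looking at imbalance. The baseline value of the primary outcome is a natural prognostic covariate, yet no sentence guarantees it a place in any model. At stake is precision that the trial could have at no cost, and clarity about what the adjusted result estimates.

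**Working it through.** **1. The plan's own figure, as an anchor.** From Sample size calculation: difference 0.9, SD 1.5, alpha 0.05, power 0.9, 48 per group. With n = 2(z_alpha + z_beta)²(SD/difference)²:

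- one-sided: 2 × (1.645 + 1.282)² × (1.5/0.9)² = 47.6, so 48;
- two-sided: 2 × (1.960 + 1.282)² × (1.5/0.9)² = 58.4, so 59.

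The stated 48 reproduces only with a one-sided alpha; the article does not state sidedness. That is a separate matter. Here it serves only to fix the setting: 48 per arm, standardised effect 0.9/1.5 = 0.6, and two-sided unadjusted power of about 0.84.

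**2. How often a baseline test is significant by chance.** For k independent variables at p < 0.05 the chance of at least one is 1 − 0.95^k:

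| k | Chance |
|---|---|
| 5 | 23% |
| 8 | 34% |
| 10 | 40% |
| 13 | 49% |
| 15 | 54% |

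The article's outcome and modifier sections support a count near 13: PSFS, RMQ, chronic pain grade, finger-to-floor distance, two-point discrimination, movement control tests, trunk extension and trunk flexion endurance, two fear-avoidance scores, age, gender and previous episodes. Several of these measure related things, so they are positively correlated and the true chance is lower than the independent figure.

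**3. What imbalance selection does to the adjusted test.** Simulation: 48 per arm, eight independent normal baseline covariates with equal effects, linear models, two-sided 0.05, 20,000 runs per setting. The number of covariates, their independence and R² (the share of outcome variance they explain jointly) are assumptions; the article gives none of them. The selection rule tested, entry if baseline p < 0.05, is also an assumption.

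| | R² 0.10 | R² 0.25 | R² 0.50 |
|---|---|---|---|
| Type I error, unadjusted | 0.049 | 0.050 | 0.050 |
| Type I error, fixed in advance | 0.050 | 0.050 | 0.049 |
| Type I error, chosen by imbalance | 0.047 | 0.045 | 0.038 |
| Power, unadjusted | 0.83 | 0.83 | 0.83 |
| Power, fixed in advance | 0.84 | 0.89 | 0.975 |
| Power, chosen by imbalance | 0.83 | 0.83 | 0.84 |

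The Mann-Whitney test in the same design has power of about 0.81 to 0.82. At least one covariate was selected in 33% to 34% of runs, matching step 2 for k = 8.

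**4. Is that range of R² plausible for baseline PSFS alone?** Let r be the correlation of baseline with follow-up PSFS, with equal variances at both times. If the SD of 1.5 refers to follow-up scores, baseline explains r². If it refers to change, baseline explains (1 − r)/2 of the change, and adjusting change for baseline gives the same treatment estimate as adjusting follow-up for baseline. For assumed r of 0.3, 0.5 and 0.7 the first gives 0.09, 0.25 and 0.49; the second gives 0.35, 0.25 and 0.15. Both lie within about 0.10 to 0.50.

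**The case against.** The strongest reply is that the mechanism is inferred. The article gives no p-value threshold for entering a covariate and nowhere says that a variable with a non-significant baseline test is left out. A reader might infer that baseline PSFS would be dropped whenever its test is non-significant; the text does not say so. The regression sentence could also describe a sensitivity analysis. This stands, and it is why the point is put as the natural reading and not as a stated rule.

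A reader might also infer that imbalance-driven adjustment inflates type I error. It does not: selection makes the adjusted test slightly conservative. Only reporting the smaller of the unadjusted and adjusted p-values raises the error rate, to about 0.054 to 0.056, and the article plans no such thing.

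Nor is it right that the baseline tests contaminate the group comparison. The Mann-Whitney test is unaffected by them, and the wording gives it the role of comparing the groups and the regression the role of assessing influence. What remains is that neither is labelled the main treatment comparison.

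It is tempting to say that about half of such trials would trigger adjustment. That needs both independent variables and the unwritten entry rule.

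The covariate list in Treatment effect modifiers is some defence, since it was chosen for relevance. But it only allows control, fixes no model, omits baseline PSFS and includes a post-randomisation item.

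Finally, a full covariate list is commonly left to an analysis plan that is not shown. Its absence alone would be no finding. The point rests on what the article does state: baseline tests, and a regression framed by the differences observed.

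**Conclusion.** The concern holds in limited form. The baseline significance tests are stated and uninformative. The regression is framed around observed differences, so on its natural reading adjustment follows imbalance and not prognostic strength, and nothing secures adjustment for baseline PSFS.

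The cost is precision. With a standardised effect of 0.6 and 48 per arm, imbalance selection leaves power about where no adjustment leaves it. The loss against a model fixed in advance is negligible at R² 0.10, about 6 percentage points at 0.25 and about 13 at 0.50. These sizes depend on eight equal, independent covariates, the assumed R² and the assumed entry rule. The chance of at least one significant baseline difference is 34% to 54% for 8 to 15 independent variables, and lower if they are correlated. This does not threaten the trial's validity, but it is worth correcting because the correction is nearly free.

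**What to change.** 1. Report baseline characteristics by arm descriptively and remove the comparability tests.
2. Replace the regression sentence with a prespecified model: follow-up PSFS on treatment, baseline PSFS and a short fixed list of baseline variables already collected, for example RMQ and fear-avoidance beliefs. Fit it whatever the observed balance.
3. Exclude anything measured after randomisation from that model, home exercise in particular.
4. State whether this model or the Mann-Whitney test is the main treatment comparison, and what role the other has.

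Centre need not be a covariate. The article gives 12 sites in the abstract and 13 in the Design section, which is about 106/12 = 8.8 or 106/13 = 8.2 patients per site, and states no stratification by site. Including it is a debatable trade-off.

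The cost is a change of wording before the data are analysed. No new data are needed, fewer tests are run, and the planned 106 patients are unchanged.

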### Blinding

Patients and therapists cannot be blinded to treatment. To keep patients unaware of any expected treatment group benefit, patients will be informed that the effect of two well-established therapies is to be evaluated. An independent and blinded assessor will record videos of the movement control tests at the end of the treatment phase and perform the post-treatment physical examination. A second blinded assessor will rate the video recordings of the MCI tests. Statistical analysis will be blinded regarding treatment group code. The researcher who will perform the statistical analyses will not be involved in taking the measurements.

## Results

Inclusion of patients began in July 2010 and is expected to last until the end of 2011. Results are expected in 2013.

## Discussion

This randomised controlled trial will compare the effectiveness of two exercise-based physiotherapy treatment protocols in a well-defined subgroup of NSLP. Inclusion is based on the clinical diagnosis of MCI with clinical tests shown to be reliable. The MCI tests allow easily applicable selection of participants. We will evaluate whether a treatment protocol addressing movement control problems is more beneficial than a general exercise protocol.

The multicentre design of the study allows treatment by different physiotherapists and improves generalisability. The selection of patients reflects the population usually found in different clinical settings. Randomisation is organised centrally and prevents selection bias.

Both treatment protocols are widely used and well-established in physiotherapy. The physiotherapists treating each group are equally instructed and experienced in applying the respective treatments. This prevents a disadvantage for the participating patients regarding group allocation.

Blinding the therapists is generally not possible. To minimise measurement bias, the measurements taken after the treatment will be taken by an assessor not involved in the treatment procedures.

The results of this study will provide evidence to improve the selection of exercise treatments for patients with NSLBP and MCI. Results will also contribute to the understanding of the mechanisms behind MCI and its relation to low back pain.

## Abbreviations

CPG: Chronic pain grade; GCPS: Graded chronic pain scale; MCI: Movement control impairment; MI: Movement impairment; NSLBP: Non-specific low back pain; ÖMPQ: Örebrö musculoskeletal pain questionnaire; PSFS: Patient specific functional scale; RCT: Randomised controlled trial; RMQ: Roland Morris disability questionnaire; TPD: Two point discrimination
